## Abstract

**Background:**

Asthma is a common lung condition that cannot be cured, but it can usually be effectively managed using available treatments. Despite this, it is widely acknowledged that 70% of patients do not adhere to their asthma treatment. Personalizing treatment by providing the most appropriate interventions based on the patient’s psychological or behavioral needs produces successful behavior change. However, health care providers have limited available resources to deliver a patient-centered approach for their psychological or behavioral needs, resulting in a current one-size-fits-all strategy due to the nonfeasible nature of existing surveys. The solution would be to provide health care professionals with a clinically feasible questionnaire that identifies the patient’s personal psychological and behavioral factors related to adherence.

**Objective:**

We aim to apply the capability, opportunity, and motivation model of behavior change (COM-B) questionnaire to detect a patient’s perceived psychological and behavioral barriers to adherence. Additionally, we aim to explore the key psychological and behavioral barriers indicated by the COM-B questionnaire and adherence to treatment in patients with confirmed asthma with heterogeneous severity. Exploratory objectives will include a focus on the associations between the COM-B questionnaire responses and asthma phenotype, including clinical, biological, psychosocial, and behavioral components.

**Methods:**

In a single visit, participants visiting Portsmouth Hospital’s asthma clinic with a diagnosis of asthma will be asked to complete a 20-minute questionnaire on an iPad about their psychological and behavioral barriers following the theoretical domains framework and capability, opportunity, and motivation model. Participants’ data are routinely collected, including demographics, asthma characteristics, asthma control, asthma quality of life, and medication regime, which will be recorded on an electronic data capture form.

**Results:**

The study is already underway, and it is anticipated that the results will be available by early 2023.

**Conclusions:**

The COM-B asthma study will investigate an easily accessible theory-based tool (a questionnaire) for identifying psychological and behavioral barriers in patients with asthma who are not adhering to their treatment. This will provide useful information on the behavioral barriers to asthma adherence and whether or not a questionnaire can be used to identify these needs. The highlighted barriers will improve health care professionals’ knowledge of this important subject, and participants will benefit from the study by removing their barriers. Overall, this will enable health care professionals to use effective individualized interventions to support improved medication adherence while also recognizing and meeting the psychological needs of patients with asthma.

**Trial Registration:**

ClinicalTrials.gov NCT05643924; https://clinicaltrials.gov/ct2/show/NCT05643924

**International Registered Report Identifier (IRRID):**

DERR1-10.2196/44710

## Introduction

### Background

Asthma is a common lung condition affecting over 5.4 million people in the United Kingdom. For some people, it can affect daily activities and lead to life-threatening consequences [1]. Asthma cannot be cured, but it can usually be effectively controlled with available treatments, provided they are taken as recommended [1]; however, it is well recognized that up to 70% of patients do not take their asthma treatments as recommended (ie, they are nonadherent) [2]. This is perhaps not unexpected in the context of a chronic condition requiring daily treatments, which must be taken even when the person feels well [3]. People may also have concerns about using long-term medicines (including steroid inhalers), or there may be other psychological or behavioral barriers to adherence [4]. Nonadherence to asthma treatments results in poor asthma control with persistent asthma symptoms, more frequent asthma attacks, and greater impairment in quality of life [5]. There are also significant economic implications associated with “wasted” medications and additional health care requirements, such as doctors’ appointments and visits to the accident and emergency department, which contribute to the overall cost of asthma care in the United Kingdom, exceeding £1 billion (1£=US $1.103) per year [6].

Health care professionals play an important role in engaging and educating patients about the importance of their asthma treatments, monitoring asthma control, and identifying whether a patient is adherent or not [7]. Adherence is a complex process for the patient, who must be able to start prescribed medications, take the medications as prescribed (correct dose, inhalation technique, and frequency), and be persistent (obtaining refills to maintain adherence over time) [8]. There are limited resources available in a busy health care setting to ensure a complete understanding of each individual’s psychological and behavioral barriers, with a one-size-fits-all approach obtaining limited success [9]. As such, there is a persistent unmet need for a tool that can effectively identify these barriers to adherence in a clinical setting, allowing health care professionals to provide effective personalized treatments for nonadherence in patients with asthma.

Asthma adherence research has been able to identify population-specific psychological or behavioral needs, including (1) partnership between patient and health care professional [8], (2) issues around medication, (3) education about asthma and its management, (4) health beliefs, (5) self-management interventions, (6) comorbidities, (7) mood disorders and anxiety, (8) social support, (9) nonpharmacological methods, (10) access to health care, and (11) professional factors. However, in the clinical field, such knowledge is relatively limited, with findings only showing that people with asthma are vulnerable to adherence problems and that targeted adherence interventions to facilitate population-specific barriers are not always effective. Thus, beyond identifying the vulnerability to nonadherence and targeting known barriers, a patient’s personal psychological needs must be understood with in-depth and detailed insight. In addition, there is a need to establish which techniques, tools, or services are likely to successfully promote individualized ways to encourage behavioral change and adherence optimization.

In a clinical setting, health care professionals only have the resources to identify whether a patient is adherent or nonadherent to treatment; as a result, they are responsible for engaging and educating patients about the importance of their asthma treatments and monitoring asthma control. This assessment does not consider the individual barriers to each patient’s adherence, and the one-size-fits-all strategy is not optimum. However, because the patient’s complete picture is not presented (due to lack of feasibility, such as health care professionals’ time), health care professionals lack the resources to empower the patient to address their psychological needs. Therefore, a practical resource is needed for the health care provider to receive a 360-degree picture to help personalize each patient’s treatment effectively.

### The Theory

It is important that the psychological needs of patients can be easily assessed to allow for the patient’s personal needs to be understood, promoted, improved, and supported [10]. When focusing on adherence behavior, the currently available tools are questionnaires, but these are long and complex to complete. The capability, opportunity, and motivation model of behavior change (COM-B) model is a new questionnaire that is shorter and easier for patients to complete [11]. It involves 3 key components: capability, opportunity, and motivation [12]. This theoretical approach has not been used extensively for people with asthma. However, COM-B is meant to be comprehensive, concise, and applicable to all behaviors. The COM-B is designed to serve as a starting point for selecting interventions that are most likely to be beneficial, and particular interventions to address each component have been identified [13].

The model suggests that at any time, a particular behavior will occur when the person concerned has the capability and opportunity to engage in the behavior and is more motivated to enact the behavior over other competing behaviors. Having high COM would lead to the successful performance of behavior (see Figure 1 for a visual representation of the COM-B for adherence [14]). COM-B is designed to provide an overarching model that captures all the factors known to influence behavior change: physical capability, psychological capability, physical opportunity, social opportunity, reflective motivation, and automatic motivation [15]. Its origin can be found in the 14 domains of the theoretical domains framework (TDF: see Table 1). The TDF is an overall theoretical framework consisting of 14 domains that integrate components from numerous health behavior change theories; hence, these 14 domains are regarded as essential aspects of behavior change in health psychology. The TDF can be used to help discover the elements influencing a certain behavior without overlooking key factors. As a result, the COM-B model comprises components that are hypothesized to drive behavior. Additionally, the COM-B can be placed at the heart of the behavioral change wheel (see Figure 2); thus, this framework can be used as a mapping system [16].

Despite the COM-B model being widespread, there is only one generic self-evaluation questionnaire to assess people’s perceptions of capabilities, opportunities, and motivations intended for use in multiple behaviors and a range of diverse populations [13]. Although there was evidence of this questionnaire’s acceptance, validity, and reliability, this questionnaire has not been used with patients in a medical setting. As a result, this study will be able to further demonstrate the questionnaire’s usefulness and reliability.

**Figure 1 figure1:**
[figure not shown]
Application of the capability, opportunity, and motivation model of behavior change to adherence [16].

**Table 1 table1:** Capability, opportunity, and motivation model of behavior change and the 11 domains of the theoretical domains framework mapped out [10].

Components of the capability, opportunity, and motivation model of behavior change			Domains in the theoretical domains framework
**Capability**			
	Psychological	Knowledge Skills Memory, attention, and decision processes Behavioral regulation	
	Physical	Skills	
**Opportunity**			
	Social	Social influences	
	Physical	Environmental context and resources	
**Motivation**			
	Reflective	Social or professional role and identity Beliefs about capabilities Optimism Beliefs about consequences Intentions Goals	
	Automatic	Social or professional role and identity Optimism Reinforcement Emotion	

**Figure 2 figure2:**
[figure not shown]
The behavioral change wheel, capability, opportunity, and motivation model of behavior change at the center [15].

### Overview

This study will assess whether the brief COM-B questionnaire can identify the same psychological and behavioral barriers as the current longer questionnaires (barriers to medication adherence questionnaire) and therefore assess the COM-B questionnaire’s ability to identify any important factors that may need to be addressed to support patients to take their asthma treatments as recommended.

We will also see whether there are any links between the type and severity of asthma that someone has, their other medical problems, how much treatment they have to take each day, and the COM-B questionnaire responses. This may help us better identify people who may struggle to take their medications properly and why. Again, we will use information routinely collected in the clinic, including lung function test results and medication prescription reviews, to do this.

## Methods

### Overview

This study will employ a cross-sectional survey design focusing on adherence to asthma treatment. It will be delivered through REDCap, a web-based platform. Participants will be recruited when attending their routine clinical review with the asthma service or while an inpatient at Queen Alexandra Hospital in Portsmouth, United Kingdom. Routinely collected patient data, including demographics, asthma characteristics, asthma control, and medication regime that is already collected as part of their clinical review, will be recorded on an electronic data capture form (e-CRF) through the REDCap platform. They will then be asked to complete the series of questionnaires, all completed on the web. Patients will also be provided with a paper copy of each questionnaire. When the questionnaire is completed, the user will be provided with debriefing information.

Participants will be asked to complete a set of questionnaires that will assess the following:

Psychological and behavioral barriers that may affect the participant being able to take their asthma treatments as recommended: the brief COM-B questionnaire (which is being validated as part of this study) and the 61-item Theoretical Domain Framework Questionnaire.Their asthma symptoms and how well controlled their asthma is (Asthma Control Questionnaire [ACQ-6]), the impact their asthma has on their quality of life (Mini Asthma Quality of Life Questionnaire), and the level of anxiety or depression they may be experiencing (Hospital Anxiety and Depression Scale). All of these questionnaires are used routinely at clinic reviews.Their use of technology at home and any challenges they face with this: Digital Readiness Questionnaire.

The COVID-19 pandemic has changed the way people with asthma access their care with a move to remote consultations and questionnaire completion. The COM-B questionnaire may well be suitable for this approach. However, it is essential to assess digital readiness in this population to understand whether this is feasible and inform the design of future studies if the COM-B questionnaire proves to be successful.

It should not take more than 20 minutes to complete. The questionnaires are all validated and approval has been granted for their use in this study.

### Eligibility Criteria

Participants will be drawn from a range of adults with asthma who take regular medication for their condition. The inclusion and exclusion criteria are presented in Textbox 1.

Inclusion and exclusion criteria of the study participants.
**Inclusion criteria**
Aged 18 years or aboveWilling and able to give informed consent for participation in the studyDiagnosing of asthma confirmed by a health care professional and requiring maintenance asthma treatment, including an inhaled corticosteroid.
**Exclusion criteria**
Unable to comprehend the study and provide informed consent, for example, insufficient command of English in the absence of someone who can adequately interpret.

### Sampling and Sample Size

A power calculation was conducted to determine the sample size, using the 6 components of the COM-B model that are hypothesized to drive behavior, namely physical capability, psychological capability, physical opportunity, social opportunity, reflective motivation, and automatic motivation. Using the G-power analysis for 6 predictors, a minimum of 146 participants are needed. The G-power analysis was run using SPSS to offer a sensitivity power analysis of the effect size that this sample size was sensitive to detect.

As a result, to detect a standardized effect size of Cohen ​*d*=0.43 with 80% power (α =.05, 2-tailed), G*Power suggests we would need 146 participants in independent tests. A paired sample *t* test with 30 participants would be sensitive to the effects of Cohen *d*=0.53 with 80% power (α=.05, 2-tailed). This means the study would not reliably detect effects smaller than Cohen *d*=0.53. To detect a Pearson correlation coefficient of ρ=.21 with 80% power (α=.05, 2-tailed), G*Power suggests we would need 146 participants.

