##### Primary Analysis

The primary analysis will comprise the correlation of outcomes from the brief COM-B questionnaire and the TDF questionnaire, as well as the Spearman rank correlation coefficients (ρ; strength of the relationship) and a hierarchical multiple regression analysis. For example, the capability result of the questionnaire will be compared to knowledge, skills, memory attention and decision processes, behavioral regulation, and skills. In addition, some exploratory analysis between the variables will be conducted—this will be used to derive the content validity of the brief COM-B questionnaire.

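### With 146 participants, two-tailed power is about 72% for ρ=.21 and about 73% for d=0.43, not the stated 80%

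*Protocol article*

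**What the plan says.** All the figures are in the protocol article, Sampling and Sample Size.

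- Origin of the number: "Using the G-power analysis for 6 predictors, a minimum of 146 participants are needed". No effect size or power is given for this calculation. The figures that follow are introduced as a sensitivity analysis.
- Independent groups: a standardized difference of "0.43 with 80% power (α =.05, 2-tailed") is said to require 146, in the words "G*Power suggests we would need 146 participants in independent tests".
- Paired test: 30 participants are said to be sensitive to d of "0.53 with 80% power (α=.05, 2-tailed"). The section then concludes that the study as a whole could not reliably detect anything below d=0.53.
- Correlation: "To detect a Pearson correlation coefficient of ρ=.21 with 80% power (α=.05, 2-tailed), G*Power suggests we would need 146 participants".

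Primary Analysis correlates the COM-B results with the TDF results. The methods it adds are given in these words: "as well as the Spearman rank correlation coefficients (ρ; strength of the relationship) and a hierarchical multiple regression analysis". Secondary Analysis names one-sample t tests and a within-participants ANOVA. Data Exclusion starts the analysis at 146 completed questionnaires.

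**The concern.** The correlation claim is fully specified: effect size, α, sidedness, power and N are all printed. It can therefore be checked without assumptions, and it fails. The d=0.43 claim lacks only the split between groups, and it fails even under the most favourable split.

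The correlation between the two questionnaires is the primary analysis, and ρ=.21 is the only correlation sensitivity that the protocol gives. If the true correlation were .21, the chance of missing it would be about 28%, not the 20% that a reader would take from the text. A non-significant result near that value would then be read with more confidence than the design supports.

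The d=0.53 sentence adds a second problem. It turns a result for 30 paired observations into a limit for the whole study. That limit conflicts with the d=0.43 claim beside it, and it is far from what 146 participants can detect in a paired or one-sample test.

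**Working it through.** **Inputs.** From Sampling and Sample Size: α=.05 two-tailed, power 80%, N=146, ρ=.21, d=0.43, and the paired case n=30, d=0.53. Assumed: a 73:73 split for d=0.43, because no split is stated and equal groups give the highest power. Normal quantiles: 1.960 (two-tailed 5%) and 0.842 (80% power).

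**1. The figure that reproduces.** For a paired t test with n=30 and d=0.53, the noncentrality is 0.53 × √30 = 2.903, with 29 df and critical value 2.045. The noncentral t gives power 80.1%. The method therefore agrees with the protocol on the one figure that is right.

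**2. Pearson ρ=.21 (Fisher z).**
- atanh(.21) = 0.2132 and √(146 − 3) = 11.958, with product 2.549.
- Power = Φ(2.549 − 1.960) = Φ(0.589) = 72.2%. A simulation of the exact test with 1,000,000 draws gives 72.6%.
- N for 80% = ((1.960 + 0.842)/0.2132)² + 3 ≈ 175.7, so 176. In the simulation, 175 just reaches 80%.
- Detectable at N=146: tanh((1.960 + 0.842)/11.958) = .230.

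**3. d=0.43, independent groups (noncentral t).**
- Noncentrality = 0.43 × √(73 × 73/146) = 2.598, with 144 df and critical value 1.977. Power = 73.3%.
- 85 per group gives 79.6% and 86 per group gives 80.1%, so 172 in total are needed.
- Detectable at 73:73 with 80% power: d = 0.467.

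**4. Other readings of the same claims.**

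| Reading | ρ=.21 | d=0.43 |
|---|---|---|
| Two-tailed, N=146 (as stated) | 72.2% | 73.3% |
| One-tailed, N=146 | 81.7% | 82.7% |
| One-tailed, N needed for 80% | 139–140 | 136 |
| Two-tailed, 146 per group | not applicable | 95.6% |

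No row yields 146 for 80% power, and the text says two-tailed each time.

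**5. Spearman, as planned.** With the usual variance 1.06/(N − 3), power at a Spearman correlation of .21 is Φ(2.549/√1.06 − 1.960) = Φ(0.516) = 69.7%. If instead the Pearson value is .21 under bivariate normality, the Spearman value is (6/π) × arcsin(.105) = .201 and power is 65.8%. Detectable at N=146 with 80% power: tanh(2.802 × √1.06/11.958) = .237, about .24.

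**6. One-sample or paired t test with 146 participants.** Power at d=0.43 exceeds 99.9%. The difference detectable with 80% power is d = 0.233.

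**7. Where 146 may come from.** For a six-predictor regression with f²=0.15, the noncentral F (6 and N − 7 df, noncentrality 0.15N) gives 94.9% at N=145 and 95.1% at N=146. For 80% power the same effect needs 98. So 146 is exactly the number for f²=0.15 at 95% power. Both values are assumptions; the article states neither. Steps 1 to 6 do not depend on them.

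**The case against.** The best defence concerns weight, not arithmetic. The number 146 is attributed to the six-predictor analysis, and the ρ and d figures are presented as sensitivity statements. Correcting them moves ρ from .21 to .23 and d from 0.43 to 0.47 and changes nothing in conduct or analysis. The primary analysis asks whether two instruments for overlapping constructs agree, so the size of the correlation matters more than its significance, and .21 would be weak support either way. At ρ=.30, power is already about 96% for Pearson and 95% for Spearman. For d, the section itself disclaims effects below 0.53. All of this stands and limits the seriousness. None of it makes the printed 80% correct, and the disclaimer for d rests on the wrong test and the wrong n.

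A reader might go further in three ways that the documents do not support.

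- That power falls short for every planned analysis. It does not for the one-sample and within-participant comparisons: a one-sample or paired t test has over 99.9% power at d=0.43. For the regression, no effect size is given, so nothing can be said; under the assumed f²=0.15 it would be 95%.
- That an adherent versus nonadherent comparison would do worse still because the groups would be unequal. The analysis sections name no such t test, and the nonadherence figure of up to 70% in the Background is a cited upper bound, not an estimate for this clinic.
- That 146 is known to come from a different effect size and power level. The match in step 7 is exact, but it is still an inference.

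**Conclusion.** Wrong as written, and should be fixed. The article claims 80% two-tailed power with 146 participants for two effects where the design gives about 72% (ρ=.21) and about 73% (d=0.43). The shortfall in sample size would be about 30 (176 − 146) and 26 (172 − 146) participants respectively. For the planned Spearman coefficient, power is about 70% at a Spearman correlation of .21.

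The Pearson result needs nothing beyond the printed inputs and the standard test. The d result assumes equal groups, the most favourable case. The Spearman result assumes the 1.06 variance factor. The general limit of d=0.53 is also wrong, because it holds only for a paired test with 30 participants. The finding is confined to these statements; it is not evidence that 146 is too few for the study's aims.

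**What to change.** In Sampling and Sample Size:

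1. Keep N=146 and delete the ρ=.21 and d=0.43 claims. State instead that 146 participants give 80% power (α=.05, two-tailed) for a Pearson correlation of about .23, a Spearman correlation of about .24, and d of about 0.47 between two equal independent groups.
2. State the effect size and power used in the six-predictor calculation. If they were f²=0.15 and 95%, say so; only the study team can confirm this.
3. Limit the d=0.53 sentence to a paired test with 30 participants, or replace it with the figure for 146: a paired or one-sample t test detects d of about 0.23 with 80% power. Without this step the section would still contradict the new d=0.47.

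The cost is wording and slightly less favourable correlation and group-difference figures, with no extra participants and no change to the analyses. If the team wants to keep 80% power for a Pearson ρ=.21, the alternative is about 176 participants, which is 30 more.
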